Differences exist not only regarding the formulas used to calculate Vc, but also regarding the electrical stimulation procedure to determine the radial displacement curve from which Vc is calculated. In a systematic review about the reliability of TMG, Martín-Rodríguez et al. [1] found that previous studies mainly used an inter-stimulus interval (ISI) of 10 s or 15 s to avoid fatigue or post-tetanic potentiation. But they also stated a lack of studies investigating the optimal rest interval between consecutive stimuli [1]. To our knowledge, only two studies investigated the effect of different ISI on tensiomyographic parameters so far. One study investigated the effect of different ISI (30 s, 10 s, 5 s) on Dm and Tc of the RF muscle during ten consecutive stimuli at a constant intensity (50 mA) [31]. The results showed that Tc was not significantly affected by different ISI, whereas Dm was significantly greater using an ISI of 10 s than 30 s [31]. Notably, Tc decreased significantly during ten consecutive stimuli, irrespective of the ISI, whereas Dm was not affected [31]. However, Latella et al. [32] found no significant effect of ISI (10 s, 20 s) on Dm or Tc of the biceps brachii muscle. Consequently, they concluded that an ISI of 10 s is sufficient during five consecutive stimuli [32]. However, both of the studies mentioned above did not report Vc, so the effect of ISI during repeated stimulation on Vc is still unclear.

Therefore, the first aim of this study will be to investigate the within and between-day reliability of five different formulas to calculate Vc. The second aim will be to investigate the effect of different ISI during repeated stimulation on Vc, assessed by the example of M. biceps femoris and M. rectus femoris. We hypothesize that Vc will be affected by changing ISI during ten repeated stimuli at a constant intensity of 50 mA.

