### Sample size justification

Two different calculations were made to justify the sample size for this study. First, a precision-based calculation for the ICC of Vc was based on previous reliability studies [27, 28]. For this calculation, we used RStudio, Version 1.3.959 and the "Nest"-function from the "ICC" package version 2.3.0 [40]. Assuming the lowest ICC reported of 0.92 [28], two measurements per subject and an alpha level of 0.05, we will need 18 subjects to achieve the desired precision with a confidence interval of 0.15.

Second, to estimate how many subjects we will need to detect an effect of changing the interstimulus-interval on Vc, we used the raw data provided by Wilson et al. [31]. From those data, we calculated Vc_10-90%_ = 0.8 Dm / Tc and Vc_norm_ = 0.8 / Tc (S1 Table). As only Dm and Tc were included in those raw data, we could not apply the other three formulas. We performed a two-way (ISI x measure) repeated measures analysis of variance (ANOVA) to estimate the main effect of inter-stimulus interval on Vc_10-90%_ and Vc_norm_. We obtained effect sizes using RStudio and the "eta2_to_f"-function from the "effectsize" package [41] and calculated the sample size using the "wp.rmanova"-function from the "WebPower"-package [42]. For the sample size calculation, we assumed three groups, ten measurements per subject, an effect size f = 3.1 (Vc_10-90%_) and f = 1.6 (Vc_norm_), a nonsphericity correction coefficient of 0.7 (Vc_10-90%_) and 0.6 (Vc_norm_), an alpha level of 0.01, a power of 0.95 and a between effect, a total of 9 (Vc_10-90%_) subjects and 18 (Vc_norm_) subjects were needed. We confirmed the estimated sample size for the ANOVA by repeating the calculations for both Vc_10-90%_ and Vc_norm_ using g*power v3.1.9.2 [43]. Based on the results of both calculations for the ICC and the ANOVA and accounting for potential dropouts, we intend to recruit 24 subjects.

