**Fig 2 pone.0262156.g002:**
[figure not shown]
Typical displacement curve during the twitch contraction phase until maximum displacement and tensiomyographic parameters. (A) Three generic tensiomyographic parameters: maximum radial displacement (Dm), Delay time (Td), Contraction time (Tc). (B) Mean rate of displacement from electrical stimulus until 10% of Dm (Vc_0-10%_), mean rate of displacement from electrical stimulus until 90% of Dm (Vc_0-90%_) and mean rate of displacement between 10% and 90% of Dm (Vc_10-90%_).

From these data, we will calculate (1) the mean rate of displacement during the time interval between the electrical stimulus until 10% of Dm as Vc_0-10%_ = 0.1 * Dm / Td (mm/s) [17] (Fig 2B), (2) the mean rate of displacement during the time interval between the electrical stimulus until 90% of Dm as Vc_0-90%_ = 0.9 * Dm / (Td + Tc) (mm/s) [25] (Fig 2B), (3) the mean rate of displacement during 10% and 90% of Dm as Vc_10-90%_ = 0.8 * Dm / Tc (mm/s) [17] (Fig 2B), (4) the normalized rate of displacement by dividing the mean rate of displacement during 10% and 90% of Dm by Dm as Vc_norm_ = 0.8 / Tc (1/s) [30] and (5) the ratio of Dm and the time interval from the stimulus until 90% of Dm as Vc_Dm/t90%_ = Dm / (Td + Tc) (mm/s) [29] (Fig 2A).

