Further, information on the optimal rest interval between consecutive stimuli during progressive electrical stimulation is lacking. Again, only two studies have investigated the effect of different ISI on tensiomyographic parameters [31, 32]. One study investigated the effect of different ISI (30 s, 10 s, 5 s) on Dm and Tc of the rectus femoris muscle during ten consecutive stimuli [31]. The results showed that Tc was not significantly affected by different ISI, whereas Dm was significantly greater using an ISI of 10 s than 30 s [31]. Notably, Tc decreased significantly during ten consecutive stimuli, irrespective of the ISI, whereas Dm was not affected [31]. These findings are relevant for assessing the muscle contraction velocity using Vc. An increase in Vc can be expected, if Dm increases while Tc remains unchanged as a higher displacement amplitude is achieved within the same time. Similarly, an increase in Vc can be also expected, if Tc shortens while Dm remains unchanged, as the same displacement amplitude is achieved within a shorter time. According to Wilson et al. [31], these changes in Dm and Tc during repeated stimulation may be explained by a potentiation effect. Indeed, repeated low-frequency electrical stimulation can induce post-tetanic potentiation [56], which leads to increased peak force, decreased time to peak force and increased rate of force development during an electrically evoked twitch [57]. Thus, it is conceivable that such a potentiation effect could also lead to an increase in Vc.

In contrast, Latella et al. [32] found no significant effect of ISI (10 s, 20 s) on Dm or Tc of the biceps brachii muscle, measured across three different joint angles and two days. Consequently, they concluded that an ISI of 10 s is sufficient during five consecutive stimuli to avoid the effects of fatigue or potentiation. However, both studies did not report Vc, so the effect of ISI during repeated stimulation on Vc is still unclear. Therefore, our results will contribute relevant information on methodical considerations for the determination of Vc using TMG.

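### The effect size f = 1.6 for the inter-stimulus interval on Vc_norm (0.8/Tc) does not fit the protocol's own report that the interval did not significantly affect Tc in the same data, so the ANOVA-based 18 subjects and 95% power are unsupported

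*Protocol article*

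**What the plan says.** All references are to the protocol article.

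- **Sample size justification.** For the ISI aim the authors write that "we used the raw data provided by" the earlier ISI study (reference 31). From its Dm and Tc values they derived Vc_10-90% and "Vc_norm_ = 0.8 / Tc (S1 Table"). They then ran a two-way (ISI by measure) repeated-measures ANOVA "to estimate the main effect of inter-stimulus interval on Vc_10-90%_ and Vc_norm". The resulting inputs were "an effect size f = 3.1 (Vc_10-90%_) and f = 1.6 (Vc_norm"), with nonsphericity coefficients of 0.7 and 0.6, alpha 0.01, power 0.95 and a between effect in three groups. The outputs were 9 subjects for Vc_10-90% and 18 for Vc_norm. A separate ICC precision calculation also gave 18. The recruitment target is 24.
- **Rate of displacement calculation formulas.** The definition is "Vc_norm_ = 0.8 / Tc (1/s"), which contains no Dm.
- **Introduction**, on reference 31: "Tc was not significantly affected by different ISI, whereas Dm was significantly greater using an ISI of 10 s than 30 s". The Discussion repeats this and adds: "Notably, Tc decreased significantly during ten consecutive stimuli, irrespective of the ISI".
- **Statistical analysis.** The planned test is a within-subject ANOVA with ISI and stimulus number as factors, at alpha 0.05.

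**The concern.** Two statements about one dataset do not fit together. The sample size section reports a very large ISI effect on 0.8/Tc. The Introduction and Discussion report no significant ISI effect on Tc. A reciprocal can shift an effect size a little, but should not turn a non-significant effect into a partial eta-squared of 0.72.

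Vc_norm gives the larger of the two ANOVA-based sample sizes (18 against 9), so it is the figure on which the 95% power for the second aim rests. If it is wrong, a non-significant ISI result for Vc_norm would appear to come from a strongly powered comparison when it may not. Repeating the calculation in a second program, as the authors did, checks the arithmetic but cannot detect a wrong input.

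**Working it through.** **1. The plan's own figures.** For a between effect in three groups, take df = 2 and n-3, with noncentrality f² × n × epsilon and alpha 0.01 (my understanding of the named function).
- f = 3.1, epsilon 0.7: power is 0.975 at n = 9, the first sample size to pass 0.95. The stated 9 is reproduced.
- f = 1.6, epsilon 0.6: noncentrality at n = 18 is 2.56 × 18 × 0.6 = 27.6 and power is 0.940; n = 19 is needed. The stated 18 is within what rounded inputs explain.

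The calculation is therefore sound given its inputs. The question is the input f.

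**2. What f = 1.6 implies.** Partial eta-squared = f²/(1 + f²) = 2.56/3.56 = 0.72. For a three-level within-subject factor in n participants, F = f² × (n-1) = 2.56(n-1), on 2ε and 2ε(n-1) degrees of freedom. Epsilon cannot fall below 0.5 with three levels.

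| Source n | F | p, ε = 1 | p, ε = 0.6 | p, ε = 0.5 |
|---|---|---|---|---|
| 4 | 7.7 | 0.022 | 0.055 | 0.069 |
| 5 | 10.2 | 0.006 | 0.023 | 0.033 |
| 10 | 23.0 | 0.00001 | 0.0004 | 0.001 |
| 20 | 48.6 | <0.000001 | 0.00000015 | 0.0000012 |

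So f = 1.6 can be non-significant only if the source study had four or fewer participants.

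**3. Does the reciprocal explain it?** Studies of 10 or 20 people were simulated with no ISI effect (within-person variation between blocks 5% or 10%). Among those with non-significant Tc, f for 0.8/Tc had a median of 0.19 to 0.28 and never exceeded 0.79.

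**4. Largest f that fits a non-significant result.** f_max = √(F_crit/(n-1)) at p = 0.05. For n = 10, F_crit is 3.55 (ε = 1) or 4.62 (ε = 0.6), so f_max = √(3.55/9) = 0.63 or √(4.62/9) = 0.72. The source n is not in the documents, so 10, 20 and 30 are assumptions.

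**5. Power at N = 24 for those upper bounds.** This uses the within-subject design actually planned: df 2ε and 2ε × 23, noncentrality f² × 2ε × 23, ε = 0.6. For f = 0.72 (0.716 unrounded), noncentrality is 0.716² × 27.6 = 14.1.

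| Assumed source n | f_max (ε 1 to 0.6) | Power, alpha 0.01 | Power, alpha 0.05 |
|---|---|---|---|
| 10 | 0.63-0.72 | 67-81% | 87-94% |
| 20 | 0.41-0.46 | 27-35% | 52-62% |
| 30 | 0.33-0.37 | 16-20% | 36-43% |

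These are ceilings, because they use the largest effect the reported result allows. All 24 subjects are taken to be complete.

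**6. What N = 24 can detect.** Solving the same formula at alpha 0.05, for ε from 1 to 0.6: partial f of 0.60-0.73 at 95% power, or 0.47-0.57 at 80% power.

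**The case against.** The best defence is that much is unseen. The size, model and test of the source study are not in the protocol article, and the supplementary table with the derived values is not at hand. Non-significance is not absence, and no significance test for Vc_norm itself is reported. All this stands, and it is why the power figures are given as a range on assumed source sizes. It does not remove the conflict, which needs only five source participants and a within-subject analysis, and which already allows the largest effect a non-significant test permits.

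A reader might also infer more than the documents support:
- **That f = 3.1 is equally wrong.** It is not contradicted in this way. Vc_10-90% contains Dm, and Dm did differ between 10 s and 30 s in the source study. It came by the same route and merits a recheck, no more.
- **That the source data show no ISI effect on Vc_norm.** The text reports only that Tc was not significantly affected.
- **That f = 1.6 is really the stimulus-number effect, or comes from treating stimulus means as units.** The first is plausible, since Tc fell over the ten stimuli, but neither can be established from the text.
- **That hundreds of subjects are needed.** Putting the smaller f values into the plan's three-group between formula gives totals up to about 320, but every participant here receives all three intervals. The within-subject formula (ε = 0.6, 95% power) gives 35-44, 77-95 or 120-146 at alpha 0.01 and 25-32, 57-70 or 88-107 at alpha 0.05, for source n of 10, 20 or 30. In the most favourable case 24 is nearly enough.
- **That the authors will read a null result as proof that a short interval is adequate.** Nothing in the article says so. The stated hypothesis is that ISI affects Vc, and effect sizes for pairwise comparisons will be reported.

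**Conclusion.** The point holds for Vc_norm. As written, f = 1.6 cannot be a participant-level ISI main effect on 0.8/Tc in data where ISI did not significantly affect Tc, unless the source study had four or fewer participants. The ANOVA-based 18 subjects and the 95% power for Vc_norm therefore have no support in the document. The fault is an unreconciled input, not the arithmetic.

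The conclusion rests on the article's own account of the source study being right and on a within-subject analysis there. The size of the power shortfall rests further on the assumed source n, and runs from slight (n = 10, alpha 0.05) to severe (n = 30). The ICC-based 18 for the reliability aim and the target of 24 are not called into question.

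**What to change.** Before preregistration and recruitment:

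1. Re-run the ANOVA on the source data with the ISI-by-participant error term and identify which term produced f = 1.6. Report n, F, degrees of freedom and partial eta-squared for Vc_norm. Recheck f = 3.1 for Vc_10-90% at the same time.
2. If f = 1.6 is not the participant-level ISI effect, withdraw it together with its 18 subjects and 95% power.
3. Keep N = 24, justified by the ICC calculation, and state what it can detect in the within-subject design at alpha 0.05: partial f of about 0.60-0.73 at 95% power or 0.47-0.57 at 80% power.
4. If f = 1.6 proves correct, explain how it agrees with the Tc result given in the Introduction and Discussion, or correct that account.

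The cost is one re-run of an existing analysis and a rewritten paragraph, with no extra participants. The drawback is that the stated power will probably become less favourable.

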**Fig 1 pone.0262156.g001:**
[figure not shown]
Schematic illustration of the study flow. M1, M2, M3: Measurement time points 1,2,3, respectively, mA: Milliampere, ISI: Inter-stimuli interval.

A single rater with more than three years of experience performing TMG measurements will perform all tensiomyographic measurements across two consecutive days. The individual maximum radial displacement curve of both the RF and BF will be determined two times on the first day (M1, M2), separated by a three-minute pause, and a third time on the second day (M3), 24 h after the first measurement. On the second day and three minutes after the third measurement, we will apply three blocks of ten consecutive stimuli each. The rest intervals between consecutive stimuli in each block will be 10 s, 20 s and 30 s, respectively. The rest period between block 1, block 2 and block 3 will be three minutes, respectively. We will randomize the order of the three blocks with the different ISI for each participant.

On the first day, we will familiarize all participants with the electrical stimulation procedure by applying two stimuli with a duration of 1 ms each at 20 mA and 30 mA to the RF, followed by a three-minute rest before starting the actual measurement [31]. All measurements will be taken at the same time of the day, and a constant room temperature of 21° C. Participants will be asked to refrain from caffeine intake for 2 h preceding all measurements [37] and to avoid alcohol consumption and fatiguing exercise for 24 h before the start and during the trial to counteract possible confounding. Further, participants will be asked to record their total dietary intake during the 24 h before the first appointment and replicate their intake during the 24 h before the second visit [26] (S1 Appendix).

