To assess the effects of different ISI on Vc during repeated stimulation, we will employ a within-subject repeated-measures ANOVA. The two independent variables will be ISI (10 s, 20 s, 30 s) and stimulus number (stimulus 1 to stimulus 10). The dependent variables will be Vc_0-10%_, Vc_0-90%_, Vc_10-90%_, Vc_norm_ and Vc_Dm/t90%_ for both the RF and BF, respectively. Pairwise comparisons with Bonferroni correction will applied for significant main effects. The effect size Cohen’s d will be calculated as d = M_diff_ / √SD_1_ + SD_2_ / 2 [53] for pairwise comparisons to allow comparisons between effects of different ISI and between consecutive stimuli. Thresholds for small, moderate, large, very large or extremely large effects will be 0.2, 0.6, 1.2, 2.0 and 4.0 [54].

Statistical significance will be set at alpha ≤ 0.05. Missing data will be handled by listwise deletion of cases with missing data [55]. All statistical analyses will be performed using R studio and respective packages. Upon completion of the data collection and analysis, the raw data disaggregated by sex and the analysis code will be openly available at https://osf.io/4du2j/?view_only=ee7a4afb30514cb9a2e15381282dcec8.

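### The inter-stimulus-interval sample size is calculated as a between effect across three groups, but the trial gives every participant all three intervals and tests them within subjects

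*Protocol article*

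**What the plan says.** Protocol article, Sample size justification: the effect size comes from data of an earlier ISI study. "We performed a two-way (ISI x measure) repeated measures analysis of variance (ANOVA) to estimate the main effect of inter-stimulus interval" on Vc_10-90% and Vc_norm. For the sample size, "we assumed three groups, ten measurements per subject", with f = 3.1 and a nonsphericity coefficient of 0.7 for Vc_10-90%, and f = 1.6 and 0.6 for Vc_norm. The remaining settings are "an alpha level of 0.01, a power of 0.95 and a between effect". The results are 9 and 18 subjects. The section then reports a check in a second program: "We confirmed the estimated sample size for the ANOVA by repeating the calculations". Together with a separate precision calculation for the ICC, which asks for 18, and an unquantified allowance for dropouts, the target is 24.

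The design is different. The Study design section describes a single group. Under Experimental approach, all three ISI blocks are applied on day two: "We will randomize the order of the three blocks with the different ISI for each participant". In the Statistical analysis section, for ISI (three levels) and stimulus number (ten levels), "we will employ a within-subject repeated-measures ANOVA", with significance set at 0.05.

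**The concern.** A between effect with three groups compares three separate sets of people, one per ISI, and judges the difference against the spread between people. The planned test compares three conditions in the same people and judges the difference against the ISI-by-participant variation. These tests have different error terms and degrees of freedom, so a sample size for one is not a sample size for the other.

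Two inputs also sit badly in a between-group test. The f values come from a repeated-measures ANOVA, so they are scaled to a within-person error. The nonsphericity coefficient corrects for unequal variances and correlations across repeated levels of a within-subject factor, and it has no role in a test between independent groups.

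At stake is whether the stated subject numbers and the 95% power describe the ISI test that will be run.

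**Working it through.** **Inputs** (Sample size justification): f = 3.1 with ε = 0.7 (Vc_10-90%); f = 1.6 with ε = 0.6 (Vc_norm); alpha 0.01; power 0.95; three groups. The article does not print a noncentrality formula. The one below is inferred because it comes close to the stated results.

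**Step 1. Reproduce the plan's figures as a between effect.** Noncentral F with df1 = 3 − 1 = 2, df2 = N − 3 and λ = f²·N·ε, solved for power 0.95:

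| | λ | N | stated |
|---|---|---|---|
| Vc_10-90% | 3.1² × 0.7 × N = 6.727·N | 8.5 | 9 |
| Vc_norm | 1.6² × 0.6 × N = 1.536·N | 18.5 | 18 |

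At exactly 18 subjects and f = 1.6 the power is 0.940. An unrounded f of 1.633, which the article would print as 1.6, gives 18. Other tests with three groups and ten measurements fit less well: the within effect needs 7 and 19, the interaction 8 and 24. The stated 9 and 18 are thus totals over three parallel groups, that is 9/3 = 3 and 18/3 = 6 people per ISI.

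**Step 2. What the nonsphericity coefficient does.** The same between test with ε = 1 gives 7.6 and 13.3, so 8 and 14 subjects. For Vc_norm, a coefficient that does not belong in this test moves the answer from 14 to 18–19.

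**Step 3. The planned test with the plan's own inputs.** One group of n, ISI as a three-level within-subject factor, df1 = 2ε, df2 = 2ε(n − 1), power 0.95. Two conventions for f are in use. In the first, λ = f²·n·ε, with the same dependence on f as in step 1. In the second, f² is the ratio of the ISI to the error sum of squares, as it is when f is converted from a partial eta squared. The error has 2(n − 1) degrees of freedom, so λ = f²·2(n − 1)·ε.

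| | stated | λ = f²·n·ε | λ = f²·2(n − 1)·ε |
|---|---|---|---|
| Vc_10-90%, alpha 0.01 | 9 | 5.8 → 6 | 4.7 → 5 |
| Vc_norm, alpha 0.01 | 18 | 15.2 → 16 | 9.9 → 10 |

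At the analysis alpha of 0.05, the first convention gives 5 and 11.

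**Step 4. Power of the planned test for Vc_norm**, on the less favourable first convention at alpha 0.01: 0.983 with 18 subjects and 0.999 with 24.

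**Step 5. Smallest f detectable with 24 participants** (power 0.95, alpha 0.05), for ε from 1 down to 0.6:
- λ = f²·n·ε: f about 0.83 to 1.01.
- λ = f²·2(n − 1)·ε: f about 0.60 to 0.73.

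These are the same detectable effects on two scales, so either range is uninterpretable unless the convention is named.

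**The case against.** The strongest reply is that nothing changes. At the plan's own inputs the planned test needs fewer subjects than stated, the ICC calculation asks for 18 in any case, and 24 covers both. That stands, and it limits the weight of the point. It does not make the paragraph right, because the numbers and power it gives still belong to another test.

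It can also be said that the arithmetic is sound: 9 reproduces, and 18 reproduces within the rounding of f. That stands too. The fault is a mismatch between calculation and design, not a slip in computing.

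Three stronger readings are tempting, and the documents do not support them.

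- A reader might infer that the ISI comparison is underpowered. At the stated f and ε the recalculation points the other way.
- A reader might infer that the second program cannot have returned 18, since a between test without ε needs only 14. The article does not give that program's test, options or inputs, so its output cannot be judged. For Vc_10-90%, moreover, 8 rounded up to three equal groups is 9, which matches. What can be said is that the sentence, as described, does not verify the planned test.
- A reader might use the assumed ICC of 0.92 to put a figure on the gap between the two error terms. That ICC is from an earlier between-day study of other Vc formulas (V_10 and V_90), and nothing links it to the ISI-by-participant error here. The error terms differ in kind; the documents do not show by how much.

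Nor is the lack of a stated detectable effect a fault in itself. A power-based justification need not report one.

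**Conclusion.** The point holds as an inconsistency within the article. The ISI sample size was calculated for three independent groups, while the study has one group and a within-subject test. The stated 9 and 18 subjects at 95% power are not properties of the planned analysis. At alpha 0.01 the stated numbers are about 1.1 to 1.8 times what that analysis needs (18/16 = 1.1; 9/5 and 18/10 = 1.8), so the error is conservative and 24 need not change.

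This rests on two assumptions: that the noncentrality in step 1 is the one used, which the fit to 9 and 18 supports, and that the stated f and ε apply to the within-subject ISI test. The second deserves documentation. With f² / (1 + f²), the two f values correspond to a partial eta squared of 9.61/10.61 = 0.91 and 2.56/3.56 = 0.72. The article does not say which eta squared was converted or on which scale f was entered.

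**What to change.** Rewrite the ISI part of the Sample size justification:

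1. Specify one group with ISI as a three-level within-subject factor, and apply ε to the degrees of freedom and the noncentrality.
2. Use the alpha of the planned analysis (0.05 in the Statistical analysis section), or explain why the sizing uses 0.01.
3. State how f was derived from the earlier data, including the type of eta squared, and which noncentrality convention the software applies.
4. If a detectable effect for 24 participants is reported, name its convention: about 0.83–1.01 for λ = f²·n·ε, or 0.60–0.73 for λ = f²·2(n − 1)·ε (power 0.95, alpha 0.05, ε from 1 to 0.6).
5. Repeat the second-program check for the within-subject test and give its test and inputs.

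The cost is one paragraph and a few lines of code. Recruitment, design and analysis are unchanged.
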